### Exclusion criteria:

Patients with pancreatic cancer pathologyOther cancers (excluding prior pancreatic cancer or skin cancer other than melanoma) within 5 years from eligibility screeningPregnant or nursing woman, or women of childbearing age not willing to use contraceptionProtected and vulnerable adultsIndividuals not covered by health insurancePatients unable to understand and sign written informed consent.

#### Healthy controls

After the completion of patients’ inclusion in each phase, the INOVIE Biobank (INOSPECIMENS) will graciously provide blood samples from age- and sex-matched HCs (*n* = 85 at the end of the discovery phase then *n* = 30 for the validation phase).

#### Sample size justification

DISCOVERY PHASE (85 patients with resectable PDAC and 85 HCs):

With a total sample size of 170 (*n* = 85 patients with resectable PDAC and *n* = 85 HCs), a two-sided 95% confidence level with an AUC = 0.85, produces a confidence interval width of 0.118 (distance from AUC to the limit = 0.059; nQuery software / Confidence interval for AUC).

VALIDATION PHASE (30 patients with resectable PDAC and 30 HCs):

The sample size is based on the recruitment potential from the BACAP cohort for a 12-month period of inclusion and corresponds to ~ 30% of the total sample.

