### Statistical analysis

In this project, the first type of machine learning model we will train is random forests. These will be used to predict whether a patient will develop pancreatic cancer based on all measured markers and associated health data. The dataset collected in this project will be divided into three different subsets: a training set (60% of the samples), a test set (20% of the samples), and a validation set (20% of the samples). A stratified sampling approach will be used to ensure that each class is accurately represented in each set, especially if an imbalance between classes is present in the original dataset. The training and test subsets will be used to train the machine learning algorithms, while the validation subset will be used to ensure that the model is generalizable (i.e., it can accurately classify future samples that may be collected). We will use the out-of-bag error method (a bootstrapping procedure that trains the models on multiple subsets of the predictor variables) to quantify the relative contribution of each variable to the model's performance. In addition, the performance of each model will be quantified by calculating its accuracy, precision, and area under the curve (AUC). In the performance of the random forest models is not satisfactory, the same approach will be used, but this time using XGboost and artificial neural network models instead. This approach allows the complexity of the model to be gradually increased, with the aim of forming a parsimonious model with a good ability to distinguish between healthy and cancer patients. The performance of all models trained during this project will be compared to a multiple logistic regression model as a baseline model.

We will also explore the results of machine learning models in the inferential framework. Using generalized linear models, we will compare the mean of each marker retained by the best machine learning models, while controlling for confounding variables (e.g., age…). This approach will quantify the differences in markers between healthy and cancer patients and identify markers that may not be statistically significantly different between the two groups but still contribute to good machine learning performance (those variables are called "weak predictors").

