## Discussion

The growing global prevalence of PC, which is typically detected at an advanced stage due to a lack of a biological test, compelled us to develop an effective screening method for PC detection. In its aim, our consortium consists of four academic institutions with an international track record of research on *LB* (e.g., CTCs, ctDNA, EVs), circulating microbiota and AI-based algorithms. The recruitment of patients with PDAC, pancreatic benign conditions, and HCs is under the supervision of Pr [name] (BACAP consortium) and INOVIE Biobank ([name]), respectively. Since 2015, more than 1,600 patients have been included in the BACAP cohort, with clinical, radiological, epidemiological, and social data linked to the biological samples readily available. In the last year, 100 patients were primarily included from three centers (University Hospital of Toulouse, Cancer Institute of Montpellier, and University Hospital of Lille). These patients represent 25 with resectable, 35 with borderline or locally advanced, and 40 with metastatic PDAC. Based on these inclusion data, we plan to include 215 patients with PDAC at diagnosis and before any treatment, as previously explained. Blood samples from age- and sex-matched HCs will be graciously provided by INOVIE Biobank at the end of each inclusion period.

The area of competences of our network includes: *1/ LB* platforms: *a)* the LCCRH & Liquid Biopsy lab for CTCs detection, CIC evaluation to assess the immune system status and EVs analysis in collaboration with [name] from Lisbon under the expertise of Pr [name], *b)* [name] lab for ctDNA analysis using universal methylation markers by sensitive ddPCR at the single-fragment ctDNA level, *c)* Pr [name] and [name] lab for circulating microbiota as a completely new circulating biomarker in LB, *d)* Industrial partner services supervised by Pr [name]’ lab for circulating cell-free nucleosomes (VOLITION) and circulating proteins (O-link) analysis; *2/* AI-based algorithmic analyses (after the discovery and validation phases) by [name] at the CREEC/CANECEV, MIVEGEC (CREES), University of Montpellier, CNRS, IRD, Montpellier, and statistical analyses by [name] (University Hospital Center of Montpellier, Biostatistics Department) for the calculation of the number of patients and HCs to recruit in this project.

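### The stated AUC precision of ±0.059 applies to a fixed test scored on all 85 v 85; no out-of-sample AUC in the plan attains it (about ±0.10 to ±0.13)

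*Protocol article*

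**What the plan says.** **Sample size justification.** The discovery phase is sized on the precision of one AUC. The inputs are "With a total sample size of 170" (85 resectable PDAC, 85 HCs) and "a two-sided 95% confidence level with an AUC = 0.85". This "produces a confidence interval width of 0.118 (distance from AUC to the limit = 0.059"). The 30 v 30 validation phase has no precision statement. It rests on the "recruitment potential from the BACAP cohort for a 12-month period of inclusion" and on being roughly 30% of the whole sample.

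**Statistical analysis.** The project's dataset is divided, with stratification by class, into "a training set (60% of the samples), a test set (20% of the samples), and a validation set (20% of the samples"). The first two subsets serve to train the algorithms, and "the validation subset will be used to ensure that the model is generalizable". Each model's accuracy, precision and AUC are to be calculated, but the subset is not named. Out-of-bag error is mentioned only for ranking the contribution of variables.

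**Validation phase.** The chosen combination is then tested by blinded classification of 30 patients with resectable PDAC and 30 HCs.

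**Endpoints.** The AUC of the signature is an endpoint. Sensitivity and specificity are defined for resectable PDAC against HCs.

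**The concern.** The precision figure is the only quantitative basis given for the size of the study. It treats the signature as already fixed and scored once on every one of the 85 patients and 85 controls. In the plan, the signature is built from most of those same people. The people left over to evaluate it, whether the 20% subset or the later cohort, are far fewer.

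At stake is what a reader will expect of the result. The article also plans to move from random forests to XGBoost and neural networks if performance is not satisfactory, and to compare all models with a logistic baseline. At ±0.133, an observed AUC of 0.85 runs from about 0.72 to 0.98, which is a weak basis for such choices. At ±0.059 it would run from 0.79 to 0.91.

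**Working it through.** **Inputs from the article.** AUC A = 0.85, two-sided 95% (z = 1.96), 85 v 85, a stratified 60/20/20 split, and a 30 v 30 validation cohort. Totals are 85 + 30 = 115 resectable PDAC and 85 + 30 = 115 HCs.

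**Formula (Hanley-McNeil).** SE² = [A(1−A) + (n1−1)(Q1−A²) + (n2−1)(Q2−A²)] / (n1·n2), with Q1 = A/(2−A) and Q2 = 2A²/(1+A).

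- A(1−A) = 0.1275 and A² = 0.7225
- Q1 = 0.85/1.15 = 0.73913, so Q1−A² = 0.01663
- Q2 = 1.445/1.85 = 0.78108, so Q2−A² = 0.05858
- With n per group, SE² = [0.1275 + (n−1)·0.07521]/n²

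**Results, starting with the article's own figure.**

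| Evaluation set | Bracket | SE | Half-width | Width | Ratio to 0.059 |
|---|---|---|---|---|---|
| 85 v 85 (as stated) | 6.445 | √(6.445/7225) = 0.0299 | 0.0585 | 0.117 | 1.0 |
| 30 v 30 (validation cohort) | 2.309 | √(2.309/900) = 0.0506 | 0.099 | 0.199 | 1.7 |
| 23 v 23 (20% of 115 v 115) | 1.782 | √(1.782/529) = 0.0580 | 0.114 | 0.228 | 1.9 |
| 17 v 17 (20% of 85 v 85) | 1.331 | √(1.331/289) = 0.0679 | 0.133 | 0.266 | 2.3 |

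The stated figure reproduces: ±0.0585 rounds to 0.059, and an interval built on the logit scale has a width of 0.118.

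**Sensitivity to the variance formula.** At 17 v 17 the half-width is 0.126 with an equal-variance binormal (DeLong-type) variance and 0.149 with Obuchowski's. The logit-scale interval is 0.67 to 0.94 (width 0.275). At 85 v 85 the same two variances give 0.056 and 0.067, so the ratio of 17 v 17 to 85 v 85 stays near 2.2.

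**Sensitivity to what is split.** If the held-out 20% is read as all PDAC stages in discovery against HCs (37 v 17), the half-width is ±0.101. For all PDAC against HCs plus benign conditions over the whole study (43 v 28), it is ±0.088. Neither is the resectable-against-HC contrast in the endpoints, and neither reaches ±0.059.

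**Basis of the validation phase.** 60/230 = 26% of the resectable and HC subjects, and 60/355 = 17% of everyone. The Discussion describes the last year's inclusions thus: "These patients represent 25 with resectable, 35 with borderline or locally advanced, and 40 with metastatic PDAC". At 25 a year, 30 patients take 30/25 × 12 = 14.4 months, not 12. The phase lasts 1.5 years, in which that rate yields 37.5.

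**The case against.** The best defence is that nothing in the sample size section is miscalculated and that the article is a condensed document. It never says that the reported AUC comes from 17 v 17. The subset for the AUC is unnamed, and the split is applied to the project's dataset without saying whether that means discovery only or all 355. The full protocol or SAP may settle both. A single split followed by an independent blinded cohort is also a coherent design, and that cohort gives an unbiased AUC at ±0.099. All of this stands, and it limits the point to a mismatch between two stated parts of the plan. It does not rescue ±0.059, because no reading of the held-out data reaches it.

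Three stronger readings are tempting, and the documents do not support them.

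- *The interval is always more than twice as wide as stated.* That holds only for 17 v 17. The ratios for 23 v 23 and 30 v 30 are 1.9 and 1.7.
- *The plan will report an over-optimistic AUC from the data used for fitting.* The article does not propose this. It sets aside a held-out subset and a separate cohort. An AUC on all 85 v 85 after training on most of them would be optimistic, but that is a reason not to rescue the figure that way, not something the plan says it will do.
- *The validation phase cannot recruit 30 patients.* The 14.4 months fit within the 1.5-year phase, and the 25 patients came primarily from three centres, while all consortium partners may take part.

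**Conclusion.** The point holds as a mismatch, not as an arithmetic error. The stated precision is correct for a fixed test on 85 v 85, and the design contains no out-of-sample evaluation of that size. For resectable PDAC against HCs, the expected half-width is ±0.099 in the independent cohort and ±0.114 or ±0.133 in the 20% subset, about 1.7 to 2.3 times the stated figure.

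This rests on a true AUC of 0.85, the Hanley-McNeil variance, and a stratified split that leaves 20% of each class. That the AUC would be read from the 20% subset is inferred from that subset's role as the check on generalisability; the article does not state it. The 30 v 30 figure needs no such inference.

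The slips in the basis for the validation phase (26% or 17% rather than about 30%, and 12 months against 14.4) are minor and change no decision.

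**What to change.** Before the discovery data are modelled, choose one of the following.

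- **(a) Keep the split.** State whether it covers the discovery phase only or all subjects, name the subset on which the AUC is reported, and restate the precision there: a width of about 0.27 for 17 v 17, or about 0.23 for 23 v 23.
- **(b) Replace the single split within the discovery cohort** by repeated stratified cross-validation, with marker selection and tuning inside the folds. All 85 patients and 85 HCs then contribute out-of-fold scores. Take the interval from resampling, and say that it may be somewhat wider than ±0.059.

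Either way, give the expected precision of the 30 v 30 validation AUC, about ±0.10 (width about 0.20).

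As minor corrections, state the validation share as 26% of the resectable and HC subjects (17% of 355), and reconcile the 12-month inclusion basis with the 25 resectable patients reported for the last year and the 1.5-year phase.

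The cost is wording, some computing time under (b), and a less favourable stated precision. No extra patients are needed.

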**Fig. 1 Fig1:**
[figure not shown]
Workflow of the PANLIPSY study. The PANLIPSY study is structured around three work packages. Work package 1: recruitment of PDAC patients, patients with benign pancreatic conditions and HCs; Work package 2: liquid biopsy multi-omic approach; Work package 3: Artificial intelligence-based algorithm analysis

PANLIPSY is a five-year project divided into two distinct phases: a discovery (3.5 years) and a validation phase (1.5 years), as represented in Fig. 1.

### Discovery phase

During the first 3.5 years, patients with resectable (*n* = 85), borderline or locally advanced stage (*n* = 50), metastatic PDAC (*n* = 50), and BPC (*n* = 25) will be included. Additionally, 85 age- and sex-matched HCs will be recruited at the end of this period (in-kind contribution of INOSPECIMENS from the Groupe INOVIE). All circulating biomarkers listed above will be detected in patients’ blood samples. The exploratory design is essential to precisely determine the best *LB* signature based on the cancer stage. Patients with BPC and HCs (control groups) will also be included to eliminate potential confounding markers, background noise, and misleading biological signatures. This discovery approach will also provide different *LB* signatures correlated with PDAC aggressiveness.

### Validation phase

Secondly, the defined combination of candidate biomarkers will be validated in the final year by blindly classifying ‘patients with early-stage/resectable PDAC (*n* = 30)’ from ‘HCs’ (*n* = 30).

### Data collection and follow-up

Data are collected at the patient’s inclusion, during the diagnosis process, and before any cancer treatment administration (upfront surgery, chemotherapy-radiochemotherapy, and/or surgery and/or best supportive care), and through follow-up until death. As previously defined by the BACAP protocol, clinical data collected will include: disease presentation, demographic data, baseline biology, radiology, endoscopic ultrasound, tumor staging, pathology reports, treatments, follow-up (including biological and radiological), and survival [11]. Patient follow up will be managed according to standard-of-care and will depend on the practices of each center. All these data will be collected and stored through an e-observation system at a centralized data center.

### Liquid biopsy assays

In total, 50 mL of blood will be collected in different tubes for LB assays: one CellSave® tube (10 mL), two CELL-FREE DNA BCT® preservative tubes (Streck™, 18 mL in total), and five EDTA tubes (22 mL in total) (Fig. 2).

**Fig. 2 Fig2:**
[figure not shown]
Blood collection. 50 mL of peripheral blood will be drawn and collected in eight tubes: one CellSave® tube (10 mL) for CTC detection, two CELL-FREE DNA BCT® preservative tubes (Streck™, 18 mL in total) for ctDNA analysis, and five EDTA tubes (22 mL in total) for the detection of extracellular vesicles, circulating cell-free nucleosomes, circulating proteins, circulating microbiota and biobanking

Blood sample management will be centralized at the Laboratory LCCRH – Liquid Biopsy Lab, University Medical Center of Montpellier. Whole blood components: plasma, cells and platelets, will be isolated from blood tubes. Samples, prepared following the European Liquid Biopsy Society (ELBS) guidelines (elbs.eu), will then be shipped to the different partners for *LB* analysis. Biological samples are collected and handled following a unique protocol to ensure the homogeneity of the biological resource.

### CTC detection and characterization

Among the various CTC technologies, the CellSearch® system (MENARINI) has gained considerable attention over the past years. It is the first CTC assay cleared by the US FDA and currently the gold standard for CTC detection, and the most widely used technology for prognostic purposes in clinical studies. It is based on the enumeration of epithelial cells that are separated from whole blood samples by positive enrichment using anti-EpCAM antibodies coated with magnetic beads. Specifically, the ferrofluid reagent consists of particles with a magnetic core surrounded by a polymeric layer coated with anti-EpCAM antibodies for directly capturing CTCs. After immunomagnetic capture and enrichment, fluorescent antibodies (against cytokeratin, panCK (CK8/18/19) that are expressed in the CTC cytoplasm; and against CD45 expressed at the leukocyte surface) and the nuclear dye DAPI are added for CTC identification and enumeration. CTCs are defined as EpCAM^+^/panCK^+^/DAPI^+^/CD45^−^ cells. The 4th channel allows assessing an additional marker to characterize directly CTCs at the single-cell level.

### Circulating tumor DNA

The 18 mL whole blood, collected in CELL-FREE DNA BCT® preservative tubes (Streck™, see above) will be processed within 7 days. The following steps will be performed: *(i)* centrifugation at 1600 g/10 min/18–20 °C, *(ii)* separation of plasma from buffy coat, *(iii)* plasma centrifugation at 16000 g/10 min/18–20 °C. Plasma and buffy coat will be immediately stored at -80 °C. Before cell-free DNA extraction, the sample will be defrosted at room temperature and submitted to a second centrifugation for 15 min at 2700 g. Circulating cell-free DNA (ccfDNA) will be extracted using the QIAamp® Circulating Nucleic Acid Kit (QIAGEN®, Germany) according to the manufacturer’s instructions with an elution volume of 50 µL (AVE buffer). Incubation with proteinase K will be performed for 30 min at 60 °C. Each DNA extraction batch included a blank sample (Phosphate-buffered saline, PBS). DNAs will be quantify using Qubit™ dsDNA HS Assay Kit (Invitrogen™, Waltham, MA, USA) and then immediately stored at -20 °C.

20 µL of ccfDNA extracted from plasma will be bisulfite-converted using the EZ DNA Methylation-lightning Kit (ZYMO Research), according to the manufacturer’s instructions. Bisulfite-converted ccfDNA will be eluted in M-elution buffer. Preferentially, bisulfite-converted DNA will be immediately tested by ddPCR or when needed, stored up to one week at -20 °C until ddPCR. Three controls will be used in each conversion batch, the blank PBS sample mentioned above, 10 ng human genomic DNA extracted from whole blood (pool from multiple donors, Promega) as negative control and 10 ng enzymatically universally methylated human genomic DNA (ZYMO Research, USA) as positive control. The DNA concentrations of the control DNA samples will be determined at reception using the Qubit™ DNA HS Assay Kit (Invitrogen™).

All plasma samples will be screened for the presence of methylation markers by droplet-based digital PCR (Met-ddPCR) as previously described [12]. The assay will target the detection of hypermethylation of HOXD8 and POU4F1 genes as well as a methylation-insensitive target on the albumin (ALB) gene used as an internal control of the amount of DNA analyzed in each PCR well [13]. All ddPCR assays will be performed according to the updated dMIQE guidelines [14].

### Extracellular vesicles

EVs purification/isolation from plasma will be performed using sequential steps of centrifugation and ultracentrifugation. EVs will be characterized by nanoparticle tracking analysis (NTA) using a NanoSight NS300 equipped with a red laser (638 nm) to determine particle concentration and size distribution (Malvern Panalytical, United Kingdom) and with the NTA v3.4 software, particle concentration and size distribution will be analyzed. The total protein content of EV samples will be determined using the Pierce™ BCA Protein Assay Kit (Catalog number: 23225; Thermo Fisher Scientific).

Analysis of IgG^+^ EV population: vesicle flow cytometry analyses will be performed using an anti-human IgG F(ab’)2 conjugated with Fluor 647 antibody (Abbexa abx142503, Houston, TX, United States). Subsequently, a labelling with Carboxyfluorescein Diacetate Succinimidyl Ester (CFSE – ThermoFisher Scientific LTI C34554, MA, United States) will be performed to evaluate the vesicularity of the samples. Labelled samples will then be analyzed with the flow cytometer Apogee A60-Micro-Plus (Apogee Flow Systems, United Kingdom). The acquired data will be exported and analyzed with FlowJo software v10.4.2 (FlowJo LLC, United States).

### Circulating cell-free nucleosomes

Circulating cell-free nucleosome structures will be measured using quantitative Nu.Q® Immunoassays (Belgian Volition SRL, Namur, Belgium) performed according to the manufacturer’s instructions, as reported previously [15, 16]. Briefly, the assays consist of a sandwich immunoassay which employs a capture antibody directed against a specific histone modification or variant, coupled to magnetic beads and an acridinium ester labeled anti-nucleosome detection antibody.

Each Nu.Q® immunoassays will be performed on the IDS-i10 automated immuno-analyzer system (Immunodiagnostic Systems Ltd (IDS), UK). 50 µL of plasma samples will be incubated with the detection antibody. Then, the magnetic particles beads coated with a monoclonal anti-histone modification capture antibody will be added. Finally, after a wash step, trigger solutions will be added and the light emitted will be measured by a luminometer. Results will be expressed in Relative Light Unit (RLU), and the concentrations will be evaluated using a four-parameter logistic regression of a reference standard curve. Samples will be analyzed in duplicate.

### Circulating proteins

O-link PEA is an immunoassay-based technology that relies on matched antibody pairs for dual recognition of proteins (biomarker) in biological samples. The two matched antibodies, which target the same protein, are conjugated to unique DNA oligonucleotides with a stretch of sequences complementary to each other. When the antibody pair binds to the target protein, complementary DNA oligonucleotides hybridize, and get extended and amplified by DNA polymerase. Each amplified DNA pair contains unique barcode sequences that are read using qPCR. The library includes 3000 highly validated protein assays that cover all major biological pathways.

